# Therapeutic and pharmaco-biological, dose-ranging multicentre trial to determine the optimal dose of TRAnexamic acid to reduce blood loss in haemorrhagic CESarean delivery (TRACES): study protocol for a randomised, double-blind, placebo-controlled trial

**DOI:** 10.1186/s13063-017-2420-7

**Published:** 2018-03-01

**Keywords:** Postpartum haemorrhage, Caesarean section, Fibrinolysis, Tranexamic acid, Pharmacokinetics, Plasmin, D-dimers

## Abstract

**Background:**

Postpartum haemorrhage (PPH) is the leading cause of maternal death worldwide. Tranexamic acid (TA), an antifibrinolytic drug, reduces bleeding and transfusion need in major surgery and trauma. In ongoing PPH following vaginal delivery, a high dose of TA decreases PPH volume and duration, as well as maternal morbidity, while early fibrinolysis is inhibited. In a large international trial, a TA single dose reduced mortality due to bleeding but not the hysterectomy rate. TA therapeutic dosages vary from 2.5 to 100 mg/kg and seizures, visual disturbances and nausea are observed with the highest dosages. TA efficiency and optimal dosage in haemorrhagic caesarean section (CS) has not been yet determined. We hypothesise large variations in fibrinolytic activity during haemorrhagic caesarean section needing targeted TA doses for clinical and biological efficacy.

**Methods/design:**

The current study proposal is a blinded, randomised controlled trial with the primary objective of determining superiority of either 1 g of TXA or 0.5 g of TXA, in comparison to placebo, in terms of 30% blood-loss reduction at 6 h after non-emergency haemorrhagic caesarean delivery (active PPH > 800 mL) and to correlate this clinical effect in a pharmacokinetics model with fibrinolysis inhibition measured by an innovative direct plasmin measurement regarding plasmatic TA concentration.

A sample size of 342 subjects (114 per group) was calculated, based on the expected difference of 30% reduction of blood loss between the placebo group and the low-dose group, out of which 144 patients will be included blindly in the pharmaco-biological substudy. A non-haemorrhagic reference group will include 48 patients in order to give a reference for peak plasmin level.

**Discussion:**

TRACES trial is expected to give the first pharmacokinetics data to determinate the optimal dose of tranexamic acid to reduce blood loss and inhibit fibrinolysis in hemorrhagic cesarean section.

**Trial registration:**

ClinicalTrials.gov, ID: NCT02797119. Registered on 13 June 2016.

**Electronic supplementary material:**

The online version of this article (doi:10.1186/s13063-017-2420-7) contains supplementary material, which is available to authorized users.

## Background and study rationale

This manuscript describes the background and design of the TRACES trial, with a special attention to the updated knowledge on PPH-related coagulopathy (Fig. 1).

**Fig. 1 Fig1:**
[figure not shown]
Global view of the TRACES trial conception

### The treatment of the postpartum haemorrhage-induced coagulopathy could contribute to the reduction of maternal morbidity

Postpartum haemorrhage (PPH) remains the leading cause of maternal mortality worldwide [1]. PPH mostly occurs during caesarean section (CS) due to atony and abnormal placental insertion. Haemorrhagic CS represents more than half of severe PPH. PPH-induced coagulopathy can be potentially major and contributes to the severity of PPH [2]. Coagulopathy has been observed as a major component of maternal morbidity after vaginal delivery due to uterine atony [3, 4], but also in patients experiencing intensive care admission after massive PPH [5, 6]. Early hyper-fibrinolysis can be observed at the onset of PPH and becomes maximal 2 h after the beginning of bleeding when no prohaemostatic treatment has been given [7].

Fibrinogen decrease is a central component of PPH-induced coagulopathy concomitant to D-dimer increase and factor II decrease [3, 4, 7]. Active fibrinogenolysis remains a major component of amniotic fluid embolism, fœtal death or abruptio placentae [8, 9]. Tranexamic acid (TA) (Exacyl® Sanofi, Paris, France) reduces D-dimers and the plasmin-antiplasmin (PAP) complex peak observed at PPH onset [7], as well as in abruptio placentae [10].

### Tranexamic acid reduces blood loss and transfusion need

TA reduces bleeding and transfusion need in medical and gynaecological haemorrhage, major surgery and trauma, without major side effects [11, 12].

In obstetric settings, available TA therapeutic efficiency and safety data are limited. Eight placebo-controlled, blinded, randomised trials demonstrated that the prophylactic use of TA reduced postoperative bleeding in elective non-haemorrhagic CS or after vaginal delivery [13–20]. In antepartum anaemic patients, this mild reduction was associated with a decrease in transfusion need [20].

Only one randomised controlled study (EXADELI trial) tested TA efficiency in active PPH following vaginal delivery [21]. A high dose of 4 g was administered, followed by a continuous infusion of 1 g/h. The EXADELI trial demonstrated a mild, but significant, reduction of the bleeding volume (173 mL vs 221 mL in the control group) and a significant reduction of the delay for PPH cessation measured as a blood flow of less than 50 mL per 10 min (Fig. 2) [21]. Although limited, the bleeding volume reduction was associated with a reduction of the percentage of patients developing severe morbidity, such as anaemia or haemorrhagic shock [21]. Mild side effects were observed, including nausea and visual disturbances, but no acute kidney injury nor seizure or thromboembolism were observed. Renal function was similar or even better in the TA group. Deep vein thrombosis complicated catheter insertion in two patients in the control group and three in the TA group [21]. The major point of the EXADELI trial was the strict measurement of PPH bleeding on special graduated bags and the strict respect to the French timed PPH management [22]. Concomitant administration of prohaemostatic treatments was avoided, except for untraceable PPH, enabling the observation of the natural course of PPH-induced coagulopathy. TA clinical efficiency to reduce bleeding in the haemorrhagic caesarean context has not been previously published. In the only (unpublished) Tunisian randomised, placebo-controlled trial in haemorrhagic CS, TA administration induced a reduction of blood loss and transfusion need (*p* = 0.03). Because the absence of academic literature on CS and the low level of evidence after vaginal delivery, current 2014 French guidelines for PPH management restricted the use of TA to late administration in massive haemorrhage: ‘Tranexamic acid may be of interest in PPH treatment, even if its clinical interest has not been demonstrated in an obstetrics setting. Every clinician is free to use TA. If used, the expert group suggests the administration of a 1-g dose only if PPH resists prostaglandins’ [22]. The WOMAN trial aimed to assess the impact of the early administration of TA on death and hysterectomy in women experiencing PPH [23, 24]. Between 2010 and 2016, 20,060 women with a clinical diagnosis of PPH in 21 low- and middle-income countries were included in this randomised, double-blind, placebo-controlled trial to intravenously receive either 1 g TA (*n* = 10,051) or placebo (*n* = 10,009) in addition to standard care. The WOMAN trial found that TA decreased death due to bleeding (155 (1.5%) vs 191 (1.9%), RR 0.81; 95% CI 0.65–1.00; *p* = 0.045), especially in women given treatment within 3 h of giving birth (89 (1.2%) vs 127 (1.7%), RR 0.69; 95% CI 0.52–0.91; *p* = 0.008). Laparotomy for bleeding was also reduced (82 (0.8%) vs 127 (1.3%), RR 0.64; 95% CI 0.49–0.85; *p* = 0.002) after CS and vaginal delivery. The original composite primary endpoint was not reduced (534 (5.3%) vs 546 (5.5%), RR 0.97; 95% CI 0.87–1.09; *p* = 0.65). Adverse events were not increased in the TA group vs placebo: thromboembolic events (30 (0.3%) vs 34 (0.3%)), seizures (33 (0.3%) vs 43 (0.4%)), and renal failure (129 (1.3%) vs 120 (1.2%)). One could suggest that the TA benefit on mortality may be higher in women with severe PPH, then aim to reserve TA for the more severe situations. However, the data showed that the delayed administration of TA was associated with potential harm. Thus TA, if used, should be given early and empirically as soon as a PPH is diagnosed, and before severe haemorrhage. As the study was based on robust clinical endpoints, neither blood loss estimation nor haemoglobin drop were available. There was no subgroup analysis of TA efficacy according to the volume of bleeding. Laboratory results were not included in the primary analysis but were assessed in a few centres as a part of a secondary analysis [25]. The biological effect of the high TA dose administered in the EXADELI trial was observed and compared to a non-treated haemorrhagic group and a non-haemorrhagic postpartum group. Significant excessive fibrinolysis was noted in the untreated haemorrhagic group vs the non-haemorrhagic group at PPH onset. This excessive fibrinolysis was inhibited in the TA-treated group 30 min and 2 h after TA administration, as demonstrated by the inhibition of the D-dimers and PAP increases (Fig. 3) [7].

**Fig. 2 Fig2:**
[figure not shown]
Reduction of postpartum haemorrhage duration in the high-dose-tranexamic-acid-treated group vs the untreated control group

**Fig. 3 Fig3:**
[figure not shown]
Inhibition of the natural hyperfibrinolysis by a high dose of tranexamic acid administered at the early stage of postpartum haemorrhage. ††*p* < 0.05. Panel **a** (circles) : hemorrhagic non treated group, Panel **b** (triangles): hemorrhagic TA treated group

Few other cases or case series have previously suggested the efficiency of TA to reduce maternal mortality and morbidity in placental abruption, third trimester placental bleeding or amniotic fluid embolism [10, 26].

The TRACES clinical and pharmacokinetics dose-ranging study objective will be a better understanding of the mechanisms of TA efficacy and the optimal selection of the TA dose.

### A dose-ranging study is needed for TA optimal dose and therapeutic timing assessment

The minimal effective dose of TA is not known. In major cardiac surgery, the 4-g dose followed by a continuous infusion of 1 g/h is the known efficient therapeutic dosage. However, in trauma, as in major surgery, fibrinolysis is an expected part of coagulopathy. In PPH associated with CS, although fibrinolysis appears early and is constant, its intensity is variable and most of the PPH stops after the first step of management. We hypothesis that a 0.5-g dose is sufficient to inhibit the most common fibrinolytic activity in haemorrhagic CS, while some of the CS-associated fibrinolysis is so intense that neither 0.5 g nor 1 g will be enough the inhibit the coagulopathic process.

### The choice of the different dose regimens relevant for study in the haemorrhagic caesarean section context

The higher dose of 4 g and continuous infusion was not selected because of the minor side effects observed in the EXADELI trial [21]. The TA 2-g dosage inhibited fibrinolysis after the 30th min in the treated patients in the EXADELI trial. The dose of 1 g or 10 mg/kg is commonly used prophylactically before CS, but has not yet been tested as a treatment in an actively bleeding haemorrhagic CS. Because of the lack of data on lower doses and TA pharmacokinetics, a low 0.5-g dose should also be tested.

### Study aim and originality

The aim of the study is to determine, out of two doses (a standard and a low dose) compared to placebo, the optimal and minimal dose of an intravenously administered single bolus of TA to reduce blood loss when administered during haemorrhagic CS.

The originality of the trial can be described as follows: no previous study has been published evaluating the clinical impact of TA on blood loss and transfusion need reduction during haemorrhagic CS. The determination of the optimal dose to obtain this clinical impact is of interest for clinicians in the current obstetric practice. TA concentration and innovative direct plasmin peak assessment by a simultaneous generation thrombin plasmin assay (SGTPA) are expected to provide scientific and objective data to determine the optimal dose. The dose-ranging study with a low dose is expected to describe the minimal dose able to inhibit fibrinolysis and to contribute to bleeding reduction while minimising side effects. The first pharmaco-biological observational results allows the choice of this dose ranging. No previous study has tested the low dose in the obstetric literature in either trauma-induced massive haemorrhage or major surgery.

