### Statistical method

#### Sample size calculation

The sample size computation is based on the expected difference between the placebo group and the low-dose group and available data on the TA use in active PPH.

Ducloy et al. recruited patients who experienced moderate PPH after a vaginal delivery. The treatment was a TA uniform high dose: 4 g over 1 h, then 1 g/h over 6 h. T0–T360 blood loss after inclusion was estimated at 133 ± 252 mL (mean ± standard deviation) in the placebo group and at 58 ± 96 mL in the treated arm. Kolsi et al. recruited patients who experienced moderate PPH during CS and tested a uniform TA dose of 10 mg/kg. The TA group received 10 mg/kg of TA as an induction dose within 12 min after second-line uterotonic drug onset and 1 mg/kg/h as maintenance within the two following hours. The placebo group received the same volumes of normal saline. The average of total bleeding was 1313 ± 1432 mL in the TA group vs 2089 ± 1556 mL in the placebo group (*p* = 0.03). The WOMAN trial recruited patients who experienced bleeding after vaginal delivery or CS [24]. The design of the WOMAN trial used a 1-g single TA dose. There was no volume measurement request in the study design. The recruitment concerns mostly low-resource countries and the criterion was hysterectomy and/or mortality rate. The first results led to more than 4% and 2%, respectively, of the primary criterion, 10 times higher than European morbidity rates that cannot be extrapolated.

Given that there is no available data on the impact of low TA dosage on blood-loss reduction after inclusion, and considering a maximal 50% reduction as previously observed after higher dose administration, the required number of subjects is 103 by group for a type I error of 5% and 80% power. Considering a maximum of 10% of dropouts or missing data, we will recruit 114 haemorrhagic patients by group for a total of 342 patients.

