#### Statistical analysis

Statistical analyses will be independently performed by the Biostatistics Department of University of Lille under the responsibility of [name]. Data will be analysed using SAS software (SAS Institute Inc, Cary, NC, USA) and all statistical tests will be performed with a two-tailed alpha risk of 0.05. A detailed statistical analysis plan will be written and finalised prior to the database lock. Baseline characteristics will be described for each group. The quantitative variables will be expressed as mean and standard deviation in cases of normal distribution and median and interquartile if not. The normality of distributions will be checked graphically and using the Shapiro-Wilk test. Qualitative variables will be expressed as frequencies and percentages.

For the main objective, the blood loss measured in each experimental group (low-dose and high-dose) will be compared to that of the placebo group by using an analysis of covariance adjusted for baseline blood loss volume and centre effect. In cases of non-normal distribution (except if a log-transformation could be applied to normalise the data), relative blood loss volume will be calculated and compared using a Mann-Whitney *U* test.

Analyses will be done on an intention-to-treat basis especially concerning the patients receiving a rescue dose of TA in cases of severe (>1500 mL) haemorrhage. An exploratory analysis will be performed on all the measures of the primary endpoint (T0, T30, T60, T120 and T360). We will use the linear mixed model in order to compare the evolution of the primary endpoint according to each experimental group and the placebo group. This model allows the performing of an analysis of variance (ANOVA) test for repeated measures taking into account the correlation between the repeated measures. The choice of the covariance model will be based on the AIC criteria. Post hoc analysis at each time of measure will be performed using a Bonferroni correction.

For the secondary objectives, secondary endpoints will be compared between each experimental group and the placebo group by using the chi-square test or Fisher’s exact test for qualitative parameters, and using Student’s *t* test or the Mann-Whitney *U* test for quantitative parameters. For the quantitative parameters measured at each time, we will employ the linear mixed model, as previously described for the main objective. The incidence of adverse events will be analysed in a descriptive way.

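### The aim is to find the optimal of two doses, but every stated clinical comparison is against placebo, so none estimates how 1 g differs from 0.5 g

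*Protocol article*

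**What the plan says.** Under Study aim and originality, the protocol article wants "to determine, out of two doses (a standard and a low dose) compared to placebo, the optimal and minimal dose". The title and the Experimental plan also call the study dose-ranging.

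The abstract (Methods/design) words the primary objective more narrowly: "primary objective of determining superiority of either 1 g of TXA or 0.5 g of TXA, in comparison to placebo".

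The Statistical analysis section then names the comparisons:

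- Primary: "the blood loss measured in each experimental group (low-dose and high-dose) will be compared to that of the placebo group", by analysis of covariance adjusted for baseline blood loss and centre.
- Exploratory mixed model: its purpose is to "compare the evolution of the primary endpoint according to each experimental group and the placebo group".
- Secondary: "secondary endpoints will be compared between each experimental group and the placebo group".

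The sample size follows the same pattern: "The sample size computation is based on the expected difference between the placebo group and the low-dose group". The article states no 1 g versus 0.5 g comparison, no dose trend and no criterion for calling a dose optimal.

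Study aim and originality also expects drug concentration and plasmin measurements to help determine the optimal dose. That substudy has 48 patients in each haemorrhagic group and is to be reported in a separate publication.

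**The concern.** Two comparisons with a shared placebo group show whether each dose beats placebo. They do not show whether the doses differ from each other. Two problems follow for a trial that sets out to choose between doses.

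If both doses beat placebo, which is the most likely result at the planned power when both have the planned effect, the stated analysis does not say whether 1 g adds anything over 0.5 g. If only one beats placebo, a reader will be inclined to call that dose the better one. A difference in significance is not evidence of a difference in effect, and this pattern arises fairly often by chance when the doses are equivalent.

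The consequence would be a clinical statement about the optimal dose that rests on no estimate of the dose difference.

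**Working it through.** **Inputs.** From Sample size calculation: blood loss from T0 to T360 of 133 (SD 252) mL on placebo and 58 (SD 96) mL on treatment, taken from the earlier high-dose trial after vaginal delivery; "the required number of subjects is 103 by group for a type I error of 5% and 80% power". From Statistical analysis: "all statistical tests will be performed with a two-tailed alpha risk of 0.05". The article gives no SD for the 0.5 g or 1 g arm and no expected gap between them. Both are assumptions below, shown as ranges.

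**1. The plan's own figure.** For one dose against placebo with a difference of 133 − 58 = 75 mL:

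n = (252² + 96²)(1.960 + 0.842)² / 75² = 72,720 × 7.849 / 5,625 = 101.5, so 102 per group.

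With the noncentral t (Welch), power is 0.796 at 102 and 0.800 at 103. The stated 103 is reproduced, and it is a number for a single dose–placebo comparison.

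**2. Correlation of the two placebo tests.** Both share the placebo mean, so with equal arm sizes

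ρ = SD²(placebo) / [SD²(placebo) + SD²(dose)].

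- Equal SDs in all arms: ρ = 0.5.
- SD 252 on placebo and 96 on each dose: ρ = 63,504 / 72,720 = 0.87.

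**3. How often exactly one dose is significant when both have the same true effect.** With marginal power p for each test, P(both) = Φ₂(z_p, z_p; ρ), the bivariate normal probability, and P(exactly one) = 2[p − P(both)].

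| Power of each test | P(both), ρ = 0.5 | P(exactly one), ρ = 0.5 | P(both), ρ = 0.87 | P(exactly one), ρ = 0.87 |
|---|---|---|---|---|
| 80% | 0.69 | 0.23 | 0.74 | 0.11 |
| 50% | 0.33 | 0.33 | 0.42 | 0.16 |
| 30% | 0.16 | 0.29 | 0.23 | 0.14 |

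The lower rows are not remote. The abstract speaks of a 30% reduction, which is 0.30 × 133 = 39.9 mL. With SDs 252 and 96 and 103 per group, the standard error is √(72,720/103) = 26.6 mL, the ratio is 39.9/26.6 = 1.50, and power is Φ(1.50 − 1.96) ≈ 0.32.

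**4. Precision of the missing estimate.** The 95% half-width for 1 g minus 0.5 g with 103 per arm is 1.96 × SD × √(2/103):

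- SD 96 (the treated-arm figure): 26 mL
- SD 191 (root mean square of 252 and 96): 52 mL
- SD 252 (the placebo figure): 69 mL

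The planned dose–placebo effect is 75 mL.

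**5. Power of a direct dose test, for an assumed gap.** If one dose reduced loss by 30% and the other by 50%, the gap would be 0.20 × 133 = 26.6 mL. Power at 103 per arm would be 0.51, 0.17 or 0.12 for SD 96, 191 or 252. The dose difference is therefore mainly a quantity to estimate, not one to test.

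**The case against.** Much of the case on the other side stands.

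- The abstract's primary objective is superiority of either dose over placebo, and the primary analysis does exactly that. There is no error in the primary test. The gap is between the analysis and the wider aim.
- 'Minimal', read as the lowest tested dose that beats placebo, is addressed by the 0.5 g versus placebo comparison, the one on which the trial was sized. It would be wrong to say that this part of the aim goes unanswered.
- A reader might infer that the trial as a whole cannot inform a choice of dose. The article does not support that, because it gives part of the task to the concentration and plasmin substudy. What remains is that the substudy has 48 per haemorrhagic group, recruits in daytime, is sized on D-dimer change and is reported separately. It does not estimate the difference in blood loss between doses across all 342 patients.
- A reader might also infer that the dose will be picked by which p value falls below 0.05. The article nowhere says so. The rates above show only why such a reading must be ruled out.
- Discordance of 23–33% holds only with equal SDs. With the article's 252 and 96 mL it is 11–16%. All these rates assume that the doses work equally well.
- The article promises a detailed SAP before database lock, and it may contain these contrasts. The point rests on the comparisons that the article does state, all of them against placebo.

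**Conclusion.** The point holds for 'optimal' and for the clinical analysis as stated. The comparisons listed support statements that a dose beats placebo. They give no estimate of 1 g against 0.5 g and so cannot carry a clinical claim that one of the two is optimal.

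If the doses are equally effective, exactly one is significant in about 11–23% of trials at 80% power and 16–33% at 50% power. The lower ends take SD 252 on placebo and 96 on each dose; the upper ends take equal SDs. The calculation is a normal approximation with equal arm sizes, and the dose-arm SDs are assumed because the article gives none for 0.5 g or 1 g. The 96 mL comes from a higher dose after vaginal delivery.

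This does not affect the validity of the primary test or the sample size. It should be settled before database lock because it bears on the conclusion that the trial's title announces.

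**What to change.** Either of two changes would bring aim and analysis into line.

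1. Keep the aim and add supportive analyses to the planned primary model: the adjusted 1 g minus 0.5 g difference with its 95% CI, and a linear dose contrast over 0, 0.5 and 1 g. State that any clinical 'optimal dose' statement rests on these estimates, not on comparing the two p values, and that 'minimal' means the lowest tested dose superior to placebo, if that is what is intended. The dose difference must carry the weight: for equally spaced doses and equal arms the linear contrast has coefficients −1, 0, +1, so as a contrast of group means it repeats 1 g versus placebo and describes trend only. If the log-transformed or rank-based fallback is used, give the matching dose-to-dose estimate on that scale.
2. Or restrict the stated aim to each dose versus placebo and leave the optimal dose to the substudy and later work.

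The first option costs two contrasts in a model already planned, no patients, and no change to the primary test. Its downside is precision: with half-widths of about 26 to 69 mL, the report may have to say that the two doses cannot be separated.
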